#### Sample size

Based on a previous meta-analysis reporting a frailty prevalence of 53.3% in older adults with osteoporosis, the required sample size was first calculated using a single-sample proportion estimation formula (21). With an anticipated proportion (*P*) of 0.533, an alpha (α) level of 0.05 (*Z* α/2 = 1.96), and an allowable error (*d*) set at 0.1 *P* = 0.0533, the initial calculation yielded an *N* of 343. Furthermore, for the planned multivariate logistic regression (using G^*^Power 3.1.9.7), we assumed a medium effect size (Odds Ratio = 1.6), α = 0.05, and statistical power of 0.80. This calculation indicated that a sufficient sample size for the regression analysis is less than the calculated 343. Considering a 10% non-response rate, the total sample size required is a minimum of 378 participants, which ensures adequate power for both prevalence estimation and subsequent regression analysis.

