#### Instrument

Data will be collected using the following research instruments:

The General Information Questionnaire will collect 17 variables: sex, age, height, weight, body mass index (BMI), marital status, living arrangements, educational attainment, monthly household income, medical expense reimbursement method, presence of insomnia, exercise habits, smoking status, alcohol consumption, calcium supplementation, history of falls within the previous 6 months, and 17 comorbid conditions.Edmonton Frail Scale (EFS): developed by Rolfson et al. in 2006, the Edmonton Frail Scale (EFS) provides a comprehensive assessment of frailty encompassing physical, psychological, and social domains (22). This 11-item instrument evaluates frailty across nine key domains: cognition, general health status, independence, social support, medication use, nutrition, mood, continence, and self-reported functional performance. Cognitive function is assessed using the Clock Drawing Test, while mobility is measured via the Timed Up and Go (TUG) test. Independence in activities of daily living is quantified by the number of independently completed tasks out of eight routine activities, including cooking, cleaning, and shopping. The EFS yields a total score ranging from 0 to 17, with higher scores indicating greater frailty severity. The scale is user-friendly, practical, and can be administered within approximately 10 min, making it suitable for rapid frailty screening by both healthcare professionals and trained non-professionals. Internal consistency is acceptable, with a reported Cronbach's alpha coefficient of 0.62.Activities of Daily Living Assessment Scale (ADL): the Barthel Index is a widely used instrument to evaluate activities of daily living in older adult patients. This scale comprises 10 items, including feeding, grooming, dressing, bowel control, bladder control, toilet use, transfers (bed to chair), ambulation on level surfaces, and stair climbing (23). The total score ranges from 0 to 100, with higher scores indicating greater independence in performing daily self-care tasks. Based on the total score, patients' functional status is classified into five categories: complete dependence (0–20 points), severe dependence (21–40 points), moderate dependence (41–60 points), mild dependence (61–99 points), and complete independence (100 points).Nutritional Risk Screening Assessment Scale: the Nutritional Risk Screening 2002 (NRS-2002) was developed through international collaboration among researchers from Denmark, the United Kingdom, France, and other countries. It is designed to evaluate changes in nutritional status based on parameters such as weight variation over the preceding 3 months and dietary intake during the past week (24). The scale demonstrates moderate reliability, with a Kappa coefficient (κ) of 0.67, a sensitivity of 0.86, and a specificity of 0.37.Hospital Anxiety and Depression Scale (HADS): developed by Zigmond et al. in 1983, the Hospital Anxiety and Depression Scale (HADS) is a self-administered instrument designed to evaluate anxiety and depression symptoms experienced by patients over the preceding week (25). It comprises two subscales—anxiety and depression—each containing seven items scored on a four-point Likert scale ranging from 0 to 3. The total score for each subscale ranges from 0 to 21. Scores are interpreted as follows: 0–7 denotes no clinically significant symptoms; 8–10 indicates possible presence of anxiety or depressive symptoms; and 11–21 reflects probable clinical anxiety or depression. The internal consistency reliability, expressed by Cronbach's α coefficients, is 0.879 for the total scale, and 0.806 for both the anxiety and depression subscales.Muscle Strength Assessment: muscle strength will be evaluated using a handheld dynamometer. Participants will be instructed to perform a maximal voluntary isometric contraction by gripping the dynamometer handle with their dominant hand for 2–3 s. Two measurements will be recorded, with the highest value (expressed in kilograms) retained as the final result, reported to two decimal places.Laboratory Indicators: within 24 h of admission, the following laboratory parameters will be collected: neutrophil percentage (%), hemoglobin (g/L), C-reactive protein (mg/L), serum calcium (mmol/L), and serum creatinine (μmol/L). Normal reference ranges are as follows: neutrophil percentage: 40–75%. Hemoglobin: 130–175 g/L for males, 115–150 g/L for females. C-reactive protein: 0–10 mg/L. Serum calcium: 2.11–2.52 mmol/L. Serum creatinine: 57–111 μmol/L for males, 41–81 μmol/L for females.

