#### Data analysis

All collected data will undergo quality control prior to statistical analysis using SPSS version 27. Continuous variables with a normal distribution will be presented as mean ± standard deviation, and intergroup comparisons will be conducted using independent samples *t*-tests. Continuous variables not normally distributed will be summarized as median and interquartile range, with between-group comparisons performed using the Mann–Whitney U test. Categorical variables will be expressed as frequencies and percentages, and comparisons analyzed via chi-squared tests. Ordinal data will be assessed using non-parametric rank-sum tests. A two-sided significance level of *p* < 0.05 will be adopted for all statistical tests. Variables demonstrating *p* < 0.05 in univariate analysis, along with clinically relevant covariates identified through consultation with clinical experts, will be entered into the multivariate logistic regression model.

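### The conclusion that OR 1.6 with 80% power needs fewer than 343 participants holds for a continuous predictor per SD but not for the binary factors, so the blanket claim of adequate regression power is unsupported for them

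*Protocol article*

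**What the plan says.** The Sample size section under Stage 1 sets the sample by precision of the prevalence estimate. It starts from a frailty rate of 53.3% ("Based on a previous meta-analysis reporting a frailty prevalence of 53.3% in older adults with osteoporosis") with an allowable error "set at 0.1 *P* = 0.0533, the initial calculation yielded an *N* of 343". For the logistic regression it adds a G*Power check: "we assumed a medium effect size (Odds Ratio = 1.6), α = 0.05, and statistical power of 0.80". The result of that check is given only as an inequality: "This calculation indicated that a sufficient sample size for the regression analysis is less than the calculated 343". After allowance for 10% non-response the total is 378, "which ensures adequate power for both prevalence estimation and subsequent regression analysis".

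The section does not say whether the OR is per unit, per SD or between two groups. It gives no exposure share, no R-squared with the other covariates, and no N for the regression.

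The Instrument section lists the candidate factors. Besides scores and measurements it includes sex, marital status, living arrangements, education, income and reimbursement method, and "presence of insomnia, exercise habits, smoking status, alcohol consumption, calcium supplementation, history of falls within the previous 6 months, and 17 comorbid conditions". The Data analysis section specifies two-sided testing at 0.05. It enters every factor with univariate p < 0.05 plus covariates chosen with clinical experts, and names no main predictor.

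**The concern.** The adequacy statement is made for the regression as a whole, and no single predictor is designated. It is therefore read as covering any listed factor that may enter the model. The N for a given OR depends strongly on the kind of predictor. An OR of 1.6 per SD of a continuous variable carries much more information per participant than an OR of 1.6 between exposed and unexposed groups.

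Identifying factors associated with frailty is the second stated aim, and the Discussion expects the identified factors to inform interventions and policy. If the stated power does not hold for the yes/no factors, real associations of the planned size will often be missed. A reader who has been told that power was adequate may then take a non-significant insomnia, falls or comorbidity term as evidence of no association.

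**Working it through.** **Inputs from the article.** Frailty rate P = 0.533, OR 1.6, alpha 0.05, power 0.80, N = 343 and 378 (Sample size); two-sided testing (Data analysis); list of factors (Instrument). **Assumed, because the article gives none:** exposure share B of 50, 30, 20 or 10%, and covariate R-squared of 0 or 0.2.

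**1. The plan's own prevalence figure.** 1.96² × 0.533 × 0.467 / 0.0533² = 336.6, so 337 against the stated 343, a difference of under 2% that does not affect this point. 343 × 1.10 = 377.3, so 378. If 10% of 378 are lost, 378 × 0.9 ≈ 340 remain, so 343 is a fair basis for power.

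**2. Continuous predictor, OR 1.6 per SD.** n = (z_α/2 + z_β)² / [P(1−P)(ln OR)²(1−R²)].
- (1.96 + 0.8416)² = 7.849; P(1−P) = 0.2489; (ln 1.6)² = 0.2209.
- R² = 0: 7.849 / (0.2489 × 0.2209) = 143.
- R² = 0.5: 285. R² = 0.58: 340.

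The stated conclusion (below 343) is reproduced. Simulated power at 343 is about 99% with R² = 0.

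**3. Binary factor, OR 1.6 between groups.** n = (z_α/2 + z_β)² × V / [(ln OR)²(1−R²)], with V = 1/[B p₁(1−p₁)] + 1/[(1−B) p₀(1−p₀)]. The rates p₀ and p₁ are solved so that the overall rate is 0.533 and their odds ratio is 1.6. At B = 50%, p₀ = 0.475, p₁ = 0.591 and V = 16.30, so n = 7.849 × 16.30 / 0.2209 ≈ 579. Power at N is Φ(ln OR × √[N(1−R²)/V] − 1.96).

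| Exposure (assumed) | N for 80% power, R² = 0 | Power at 343, R² = 0 | Power at 343, R² = 0.2 | Power at 378, R² = 0 | Detectable OR at 343, R² = 0 | Detectable OR at 343, R² = 0.2 |
|---|---|---|---|---|---|---|
| 50% | 579 | 58% | 49% | 62% | 1.85 | 1.99 |
| 30% | 703 | 50% | 42% | 54% | 1.98 | 2.16 |
| 20% | 936 | 40% | 33% | 43% | 2.23 | 2.49 |
| 10% | 1692 | 24% | 20% | 26% | 3.26 | 4.01 |

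**4. Sensitivity.**
- A two-proportion formula gives N = 574, 692, 914 and 1638, with nearly the same power. Simulation at 343 gives 59% at 50% exposure and 38% at 20%.
- With 53.3% taken as the rate in the unexposed, N is 592 at 50% exposure.
- At 37.8% frailty, the figure in the Introduction, N is 614 and power 55% at 50% exposure.
- One-sided testing, contrary to the Data analysis section, still needs at least 452, with power at 343 of at most 70%.

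No binary variant examined falls below 343.

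**5. How many factors are affected.** Twelve listed items are binary or categorical: sex, marital status, living arrangements, education, income, reimbursement, insomnia, exercise, smoking, alcohol, calcium and falls. Comorbidity is added to these. Fourteen are continuous or scores: age, height, weight, BMI, ADL, NRS, two HADS subscales, grip strength and five laboratory values. With comorbidity as one variable, as the article's count of 17 does, the share is 13 of 27 (48%). With each of the 17 conditions counted separately it is 29 of 43 (67%).

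**The case against.** **The OR might be meant per SD for every factor.** The article gives no unit. A 50/50 factor has SD 0.5, so OR 1.6 per SD equals 1.6² = 2.56 between groups, and about 151 participants suffice (about 162 at 30% exposure). The arithmetic is right. But an odds ratio for a yes/no factor is normally stated and reported as exposed against unexposed, and nothing in the article tells the reader to do otherwise.

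**The quoted inequality is not an arithmetic error, and an article need not list its G*Power settings.** Both parts stand. The inequality is reproduced for a continuous predictor, and the missing settings alone would be no finding. What remains is the positive statement of adequacy for the whole regression, which the article's own OR, alpha and power do not support for many of its own listed factors.

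**Stronger readings that the article does not support.**
- A reader might infer that the regression as a whole lacks 80% power. It does not: the power is there for continuous predictors per SD, which include age, BMI, ADL, nutrition score, HADS and grip strength, unless R-squared exceeds about 0.58.
- A reader might say that two thirds of the candidates are affected. That needs every comorbidity entered as a separate term, which is not stated. Education and income may also be treated as ordinal, and only selected candidates enter the model.
- A reader might quote 40 to 58% as the power. That range belongs to assumed exposures of 20 to 50% with R-squared 0. At 343, 58% is about the ceiling, and 40% is not a floor.
- A reader might infer that the authors will call non-significant factors unrelated to frailty. The article does not say so; the risk lies in how the adequacy claim will be read.

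The sample was set by prevalence precision, and that basis is unaffected.

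**Conclusion.** The point holds in limited form: the adequacy statement is wrong as written for binary factors. With OR 1.6 between groups, such a factor needs about 579 participants under near-best conditions (50% exposure, R-squared 0). Power is then about 58% at 343 and at most about 62% if all 378 are analysed. A real association of the planned size would be missed about 40% of the time or more. The direction does not depend on the assumed exposures or R-squared, because rarer exposure and correlated covariates only lower power; the exact figures do depend on them. It rests on reading an OR for a yes/no factor as a between-group contrast. The 80% claim stands for continuous predictors per SD.

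**What to change.** In the Sample size section:

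1. Limit the 80% power claim to OR 1.6 per SD of a continuous predictor, and state the R-squared assumed.
2. Give what 343 delivers for a binary factor: a detectable OR of about 1.85, 1.98 and 2.23 at 50, 30 and 20% exposure with R-squared 0, and larger with correlated covariates (1.99, 2.16 and 2.49 at R-squared 0.2). Label the exposure shares as assumptions.
3. Delete the statement that the total ensures adequate power for the regression.

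In the Data analysis section, say that all factors will be reported with odds ratios and confidence intervals, and that a non-significant binary factor will not be read as showing no association.

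The cost is a few sentences. Recruitment and design do not change; the only downside is a less favourable stated power.

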#### Instrument

Data will be collected using the following research instruments:

The General Information Questionnaire will collect 17 variables: sex, age, height, weight, body mass index (BMI), marital status, living arrangements, educational attainment, monthly household income, medical expense reimbursement method, presence of insomnia, exercise habits, smoking status, alcohol consumption, calcium supplementation, history of falls within the previous 6 months, and 17 comorbid conditions.Edmonton Frail Scale (EFS): developed by Rolfson et al. in 2006, the Edmonton Frail Scale (EFS) provides a comprehensive assessment of frailty encompassing physical, psychological, and social domains (22). This 11-item instrument evaluates frailty across nine key domains: cognition, general health status, independence, social support, medication use, nutrition, mood, continence, and self-reported functional performance. Cognitive function is assessed using the Clock Drawing Test, while mobility is measured via the Timed Up and Go (TUG) test. Independence in activities of daily living is quantified by the number of independently completed tasks out of eight routine activities, including cooking, cleaning, and shopping. The EFS yields a total score ranging from 0 to 17, with higher scores indicating greater frailty severity. The scale is user-friendly, practical, and can be administered within approximately 10 min, making it suitable for rapid frailty screening by both healthcare professionals and trained non-professionals. Internal consistency is acceptable, with a reported Cronbach's alpha coefficient of 0.62.Activities of Daily Living Assessment Scale (ADL): the Barthel Index is a widely used instrument to evaluate activities of daily living in older adult patients. This scale comprises 10 items, including feeding, grooming, dressing, bowel control, bladder control, toilet use, transfers (bed to chair), ambulation on level surfaces, and stair climbing (23). The total score ranges from 0 to 100, with higher scores indicating greater independence in performing daily self-care tasks. Based on the total score, patients' functional status is classified into five categories: complete dependence (0–20 points), severe dependence (21–40 points), moderate dependence (41–60 points), mild dependence (61–99 points), and complete independence (100 points).Nutritional Risk Screening Assessment Scale: the Nutritional Risk Screening 2002 (NRS-2002) was developed through international collaboration among researchers from Denmark, the United Kingdom, France, and other countries. It is designed to evaluate changes in nutritional status based on parameters such as weight variation over the preceding 3 months and dietary intake during the past week (24). The scale demonstrates moderate reliability, with a Kappa coefficient (κ) of 0.67, a sensitivity of 0.86, and a specificity of 0.37.Hospital Anxiety and Depression Scale (HADS): developed by Zigmond et al. in 1983, the Hospital Anxiety and Depression Scale (HADS) is a self-administered instrument designed to evaluate anxiety and depression symptoms experienced by patients over the preceding week (25). It comprises two subscales—anxiety and depression—each containing seven items scored on a four-point Likert scale ranging from 0 to 3. The total score for each subscale ranges from 0 to 21. Scores are interpreted as follows: 0–7 denotes no clinically significant symptoms; 8–10 indicates possible presence of anxiety or depressive symptoms; and 11–21 reflects probable clinical anxiety or depression. The internal consistency reliability, expressed by Cronbach's α coefficients, is 0.879 for the total scale, and 0.806 for both the anxiety and depression subscales.Muscle Strength Assessment: muscle strength will be evaluated using a handheld dynamometer. Participants will be instructed to perform a maximal voluntary isometric contraction by gripping the dynamometer handle with their dominant hand for 2–3 s. Two measurements will be recorded, with the highest value (expressed in kilograms) retained as the final result, reported to two decimal places.Laboratory Indicators: within 24 h of admission, the following laboratory parameters will be collected: neutrophil percentage (%), hemoglobin (g/L), C-reactive protein (mg/L), serum calcium (mmol/L), and serum creatinine (μmol/L). Normal reference ranges are as follows: neutrophil percentage: 40–75%. Hemoglobin: 130–175 g/L for males, 115–150 g/L for females. C-reactive protein: 0–10 mg/L. Serum calcium: 2.11–2.52 mmol/L. Serum creatinine: 57–111 μmol/L for males, 41–81 μmol/L for females.

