## Materials and methods

### Study design

This study will employ a convergent mixed-methods approach, involving the concurrent collection of quantitative and qualitative data within the orthopedic wards of a tertiary hospital from February to December 2025. Data will be analyzed separately before integrating the results (see Figure 1).

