#### Participants

Inclusion criteria are:

(1) Age ≥ 65 years;(2) Osteoporosis Diagnosis: diagnosis of osteoporosis based on any of the following:

a dual-energy *X*-ray absorptiometry (DXA) *T*-score of ≤ −2.5 at the axial skeleton or distal one-third radius;a history of fragility fracture of the hip or vertebra;osteopenia (−2.5 < *T*-score < −1.0) accompanied by a fragility fracture of the proximal humerus, pelvis, or distal forearm (20);

(3) Possessing good communication skills, the ability to read questionnaires effectively, and intact cognitive function (e.g., scoring ≥24 on the Mini-Mental State Examination [MMSE] threshold);(4) voluntary participation with signed informed consent.

Exclusion criteria are:

(1) Patients with other critical or unstable illnesses, such as active malignant tumors or severe, acute cardiorespiratory insufficiency;(2) Patients exhibiting severe disability, bedridden status, or conditions that severely limit mobility required for frailty assessments;(3) A history of stroke or severe head trauma, or existing central nervous system diseases;(4) Individuals unable to cooperate with questionnaire surveys or frailty assessments.

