
#### Date collection

Under the supervision of the research team, standardized training on study procedures will be provided. After explaining the study's purpose and significance and obtaining informed consent, data will be collected via one-to-one interviews. For inpatients, questionnaires will be administered following their daily treatments and once they report no significant discomfort. If participants are unable to complete the questionnaire independently, the investigator will record responses based on participants' verbal reports.

Demographic data, Edmonton Frail Scale (EFS) scores, Activities of Daily Living (ADL) assessments, Nutritional Risk Screening (NRS) assessments, Hospital Anxiety and Depression Scale (HADS) scores, and muscle strength measurements will be collected through face-to-face interviews. Laboratory parameters will be retrieved from the electronic medical records system. Each questionnaire is estimated to require 15–20 min for completion. All questionnaires will be administered and collected on-site.

Following the survey, investigators will offer psychological support to participants to mitigate any distress experienced during questionnaire completion. Throughout the study, the ethical principles of autonomy, confidentiality, and non-maleficence will be rigorously upheld. Finally, all assessment results will be independently reviewed by two qualified medical professionals with a minimum of intermediate-level clinical credentials to reduce potential bias.

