The results of this study are expected to serve as a bridge between research evidence and clinical practice, offering guidance for the design of targeted interventions and the improvement of patient-clinician communication. Specifically, the findings, supported by existing literature demonstrating a strong association between frailty and vertebral compression fractures (VCFs), may contribute to the development of frailty-specific care pathways in osteoporosis management (31). At the clinical practice level, these discoveries provide a basis for establishing tailored rehabilitation programs, effective fall-prevention strategies, and needs-based nutritional interventions. For instance, by elucidating the potential complex interplay among diet-related quality of life (DRQOL), protein intake, and frailty, this research offers preliminary evidence to integrate strategies aimed at improving DRQOL and protein status, moving beyond traditional bone density-focused dietary advice. Such strategies may potentially help mitigate the progression of frailty (32). Furthermore, given the documented association between frailty and a higher incidence of multiple fractures, the study's outcomes support the necessity of routine frailty screening in all older adults with osteoporosis. On a policy level, these results can inform geriatric health strategies aimed at reducing fracture risk, functional decline, and the escalating healthcare burden associated with the bidirectional relationship between frailty and osteoporotic fractures. Ultimately, this research will contribute empirical data to support integrated management strategies and enhance the quality of life for older populations.

Furthermore, this work serves as a foundational step toward more in-depth future investigations. The successful identification of key influencing factors will provide a valuable, evidence-based foundation for wider application across diverse geographical settings and patient populations. The anticipated results will inform the development and implementation of targeted interventions, offering robust empirical evidence to support clinical practice and health policy formulation. Ultimately, this research has the potential to enhance healthcare delivery, improve quality of life for older adults with osteoporosis, and reduce frailty-related complications at both the clinical and population levels.

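### The falls item is asked during an orthopaedic admission without setting apart the fall that led to it, so the falls–frailty association may partly reflect admission after a fall

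*Protocol article*

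**What the plan says.** Study design places data collection "within the orthopedic wards of a tertiary hospital from February to December 2025". Under Instrument, the laboratory values are tied to the admission: "within 24 h of admission, the following laboratory parameters will be collected". Under the data collection heading of Stage 1: "For inpatients, questionnaires will be administered following their daily treatments and once they report no significant discomfort". The survey is thus linked to a hospital stay.

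Under Participants, one route to the osteoporosis diagnosis is "a history of fragility fracture of the hip or vertebra". Another is osteopenia "accompanied by a fragility fracture of the proximal humerus, pelvis, or distal forearm". Neither sets a minimum time since the fracture. A T-score at or below −2.5 also qualifies without any fracture. An exclusion criterion removes patients with severe disability, "bedridden status, or conditions that severely limit mobility required for frailty assessments".

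The General Information Questionnaire is said to collect 17 variables, the last two being "history of falls within the previous 6 months, and 17 comorbid conditions". Counting the comorbid conditions as one entry, the list does come to 17. Reason for admission and current fracture are not on it, nor in the other instruments.

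Under Data analysis, variables with p < 0.05 in univariate tests, plus covariates suggested by clinical experts, enter the logistic model. The Discussion names "effective fall-prevention strategies" among the practical uses expected of the findings.

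**The concern.** The look-back is not anchored before the event that brought the patient to the ward. If a patient admitted after a fall counts that fall, the answer is yes whatever happened in the preceding months. The variable then mixes two things: having been admitted after a fall, and having fallen earlier. With no reason-for-admission item, nothing in the listed data can separate them.

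The outcome is exposed to the same event. The EFS includes a Timed Up and Go test and a count of daily tasks done independently, and a current injury can worsen both. One injury could therefore raise the recorded exposure and the frailty score together.

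At stake is one candidate factor under the second study aim, identifying factors associated with frailty. If the share admitted after a fall is similar in frail and non-frail patients, a real association for earlier falls is diluted. If that share differs, an association for earlier falls can appear or reverse. This is a bias in the estimate, so a larger sample does not reduce it.

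**Working it through.** The plan gives no figure for falls or for fall-related admissions, so there is none to reproduce. The only plan figures used are the anticipated frailty prevalence (53.3%) and the planning effect for the regression (OR 1.6), both from Sample size. All other inputs are assumptions.

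**Calculation 1: what the item would record**

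Let s be the share of a frailty group admitted after a fall and p the share with an earlier fall. Assume that the two are independent within each group and that the admission fall is counted. The proportion coded as fallers is then s + (1 − s)p.

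*Dilution.* Assume p = 0.40 in frail and 0.20 in non-frail patients. The OR for earlier falls is (0.40/0.60)/(0.20/0.80) = 2.67. With the same s in both groups:

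| s | Frail, coded | Non-frail, coded | Coded OR |
|---|---|---|---|
| 0.3 | 0.3 + 0.7 × 0.4 = 0.58 | 0.3 + 0.7 × 0.2 = 0.44 | 1.76 |
| 0.5 | 0.5 + 0.5 × 0.4 = 0.70 | 0.5 + 0.5 × 0.2 = 0.60 | 1.56 |
| 0.6 | 0.6 + 0.4 × 0.4 = 0.76 | 0.6 + 0.4 × 0.2 = 0.68 | 1.49 |

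*No association for earlier falls.* Assume p = 0.20 in both groups, with s = 0.6 in frail and 0.4 in non-frail patients. The coded proportions are 0.6 + 0.4 × 0.2 = 0.68 and 0.4 + 0.6 × 0.2 = 0.52, so the OR is (0.68/0.32)/(0.52/0.48) = 1.96. With the two values of s exchanged it is 1/1.96 = 0.51. With equal s it is 1.00.

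*The independence assumption.* It affects the dilution figures. In the extreme case at s = 0.5 where every earlier faller is also a fall admission, the coded proportion is 0.50 in both groups and the coded OR is 1.00 instead of 1.56.

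**Calculation 2: cross-check with frailty fixed at 53.3%**

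Let a be the overall share admitted after a fall (0.2 to 0.6), f the frequency of earlier falls (0.2 or 0.3), and g the OR of frailty for fall admission against other admission (1 to 3). Earlier falls are unrelated to frailty.

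The frailty proportions q0 (other admission) and q1 (fall admission) solve (1 − a)q0 + a·q1 = 0.533 with odds(q1) = g × odds(q0). Frailty among recorded fallers is [a·q1 + (1 − a)f·q0]/[a + (1 − a)f]. Among recorded non-fallers it is q0.

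Example: a = 0.4, f = 0.2, g = 2 gives q0 = 0.465 and q1 = 0.635. Recorded fallers make up 0.4 + 0.6 × 0.2 = 0.52 of the sample. Frailty among them is (0.4 × 0.635 + 0.12 × 0.465)/0.52 = 0.596, and the coded OR is 1.69 before rounding of the inputs.

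| g | Coded OR over the ranges of a and f |
|---|---|
| 1 | 1.00 |
| 1.5 | 1.20 to 1.43 |
| 2 | 1.36 to 1.84 |
| 3 | 1.60 to 2.62 |

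Fall admissions make up between 0.2/0.44 = 45% and 0.6/0.68 = 88% of recorded fallers. The two calculations agree: s = 0.6 against 0.4 corresponds to g = (0.6/0.4)/(0.4/0.6) = 2.25, and the resulting 1.96 fits between the rows for g = 2 and g = 3.

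**The case against.** The strongest reply is that the article gives a variable name, not the wording of the question. It does not say whether the window runs back from interview, admission or injury, and the questionnaire, which is not shown, may settle this. That stands as a limit: a reader might infer that the plan counts the admission fall, but the plan leaves it open. It does not dispose of the point, because the article states a complete list of 17 variables and reason for admission is not among them. Experts may add covariates at the analysis stage, but they cannot adjust for something that was not recorded.

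A reader might also infer that the falls association will simply be a marker of why patients were admitted. The documents do not support that. The share admitted after a fall is unknown, patients can qualify on T-score alone, qualifying fractures need be neither recent nor due to a fall, and the mobility exclusion removes some patients with acute fractures. Earlier falls still contribute to the item.

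A further fair objection is that a fall leading to admission is a real fall within six months. In the null scenario, 1.96 correctly describes any fall in this sample; it misleads only if read as the association for earlier falls. Replacing the variable outright would have its own cost, since patients whose only fall led to admission would become non-fallers. The fix has to allow for this.

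Finally, the limitations concede selection bias, a single site and association only, but in general terms that do not reach this item. It is also fair that fall prevention appears in a general list of uses. The plan does not rest that advice on this one coefficient.

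**Conclusion.** The point holds in a limited form. The item is collected during an orthopaedic admission, its window as worded takes in a fall that led to that admission, and the listed variables cannot separate the two kinds of fall. The falls–frailty association may therefore partly reflect admission after a fall.

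Size and direction cannot be derived from the documents. Under the assumptions of Calculation 1, an OR of 2.67 for earlier falls would be coded as about 1.5 to 1.8, and an OR of 1.0 as anything from about 0.5 to 2.0. If fall admission is unrelated to frailty, an OR of 1.0 stays at 1.0. In the cross-check the coded OR reaches 2.6 at the strongest assumed link. The distortion can thus be as large as the OR of 1.6 used for planning, but nothing shows that it will be. It concerns one candidate factor under the second aim. It is worth correcting because the remedy is small and because earlier falls that go unrecorded at interview cannot be recovered by modelling.

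**What to change.** - Reword the item to ask about falls in the six months before the event that led to the current admission, leaving that event out.
- Add one yes/no item: admitted because of a fall.
- Enter the two as separate candidate factors. Patients whose only fall led to admission are then identified by the second item and are not treated simply as non-fallers.
- Report any fall in six months, including the admission fall, as a sensitivity analysis.
- When interpreting the fall-admission term, note that the injury itself can worsen the Timed Up and Go and independence items of the EFS. Separating the variables does not remove this.

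The cost is one reworded question, one added item and one extra model term, with no additional visit. In the dilution example, the reworded item would record 0.40 against 0.20 directly and so return the OR of 2.67.
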